#### Sample size calculation

The total sample size for this study (including participants at both MDJH and MDUM) is *N* = 320. With 160 participants in each arm given the hypothesized follow-up in control group of 70%, we will have 80% power to detect a difference between the study arms if the follow-up rate is 83% in the intervention group, and 90% power to detect a difference between study arms if follow-up in intervention group is 85% (Fig. 2). The hypothesized follow-up in the control group is derived from historical follow-up percentages at MDJH and MDUM.

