### Study design

This trial is designed as a randomized, controlled, nonblinded, two-arm, superiority trial with a 1:1 allocation ratio (NCT03090646). Patients who undergo donor nephrectomy at the Johns Hopkins Hospital Comprehensive Transplant Center (MDJH) and the University of Maryland Medical Center Transplant Center (MDUM) will be eligible for participation. The planned study recruitment period will be 4 years for MDJH and 3 years for MDUM. After consent and randomization, participants will be followed for the federally-mandated 2-year follow-up period (Fig. 1). The primary outcome will be the rate of policy-defined complete (all components addressed) and timely (within 60 days before or after the 6-month, 1-year, or 2-year postdonation date; i.e. 120-day period) submission of data at all 6-month, 1-year, and 2-year follow-up visits. The secondary outcome will be transplant hospital-level compliance with OPTN reporting requirements (submission of clinical data for 80% and laboratory data for 75% of donors) at each visit. Outcomes will be assessed separately for each follow-up time point and as a composite outcome over the study period, and will be compared between study arms following the intention-to-treat principle. We will also collect and report data related to potential logistical challenges of implementing the intervention (i.e., number of mailing attempts necessary, failed delivery attempts, incorrect or out-of-date contact information, etc.).

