### Statistical analysis

Rates of patient and center-level compliance for each 6-month, 1-year, and 2-year follow-up visit will be compared between study arms using Fischer’s exact test. Rates of patient and center-level compliance for the composite outcome of compliant 6-month, 1-year, AND 2-year follow-up visit will be compared between study arms using Pearson’s chi-squared test. All analyses will follow an intent-to-treat principle. Data will be analyzed by data analysts on the MDJH study team using Stata 15/MP for Linux (College Station, Texas).

Our primary end-points are the living donor policy defined outcomes of complete and timely 6-month, 1-year, and 2-year follow-up. The motivation for these outcomes is to align our findings with the relevant policy end-points, not to maximize statistical power. As an additional secondary aim, generalized estimating equations (GEE) will be used to estimate population-averaged changes in complete and timely follow-up over the full course of the study. This approach will allow for participants with non-policy compliant follow-up behaviors (e.g. missing 1-year follow-up but completing 6- and 2-year follow-up) to be counted towards a population average. This may provide insight on alternative designs for the living donor follow-up policy.

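### The stated 80% and 90% power fit Pearson's chi-squared test, planned only for the three-visit composite; if 70% is a per-visit rate, the Fisher tests planned for each visit give about 75% and 88%

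*Protocol article*

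**What the plan says.** The Sample size calculation section of the protocol article sets the design at 160 donors per arm, "given the hypothesized follow-up in control group of 70"%. From this it concludes that "we will have 80% power to detect a difference between the study arms if the follow-up rate is 83% in the intervention group", and claims "90% power to detect a difference between study arms if follow-up in intervention group is 85"%. The section does not say whether the 70% refers to one visit or to all three, which test was assumed, or at what significance level.

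The Statistical analysis section assigns two different tests. Patient-level and center-level rates at each "follow-up visit will be compared between study arms using Fischer’s exact test". The composite of compliance at all three visits "will be compared between study arms using Pearson’s chi-squared test". No reason is given for the difference.

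On which endpoint is primary, two sections can be read differently. Study design defines the primary outcome as submission at every one of the three visits, and then says that outcomes are assessed both visit by visit and as a composite. Statistical analysis speaks of primary end-points in the plural and lists the 6-month, 1-year and 2-year outcomes.

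**The concern.** A power statement describes a particular test applied to a particular endpoint. Here the planned test changes with the endpoint, and the power statement specifies neither. Fisher's exact test conditions on both margins of the 2x2 table, and because the data are discrete it rejects less often than its nominal level allows. At this sample size the loss is still visible. If the sample size section is meant to cover the single-visit comparisons, the planned test has less power than stated, and the chance of missing a true rise from 70% to 83% is about 25% rather than 20%.

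The loss is also avoidable at donor level. Exact tests are usually chosen when expected counts are small, which is not the case with 160 donors per arm and rates of 70% to 85%. Nor can sparse data explain the split between tests. A donor who meets the composite has met every visit, so the composite rate cannot exceed any single-visit rate.

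**Working it through.** **Inputs.** From the Sample size calculation: n = 160 per arm, control rate p1 = 0.70, intervention rate p2 = 0.83 or 0.85. From Study design: 1:1 allocation. Assumed, because the article does not state it: two-sided alpha = 0.05. A one-sided 5% test would give 87% and 94%, which does not match the stated 80% and 90%; two-sided 5% does.

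**Step 1. Reproduce the stated figures.** Pooled normal approximation, with p̄ = (p1 + p2)/2:

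power = Φ[(p2 − p1 − 1.96·s0)/s1], where s0 = √(2p̄(1 − p̄)/n) and s1 = √((p1(1 − p1) + p2(1 − p2))/n).

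- 83%: p̄ = 0.765, s0 = √(0.35955/160) = 0.04740, s1 = √(0.3511/160) = 0.04684. (0.13 − 0.09291)/0.04684 = 0.792, so power = 78.6%.
- 85%: p̄ = 0.775, s0 = √(0.34875/160) = 0.04669, s1 = √(0.3375/160) = 0.04593. (0.15 − 0.09151)/0.04593 = 1.274, so power = 89.9%.

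The unpooled form gives 79.3% and 90.4%. The stated 80% and 90% therefore come from an uncorrected two-proportion test, to within rounding.

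**Step 2. Exact power of both planned tests.** Enumerate all 161 × 161 pairs of outcomes (x1, x2), with x1 ~ Bin(160, p1) and x2 ~ Bin(160, p2). Sum their probabilities wherever the test rejects: Fisher two-sided p ≤ 0.05, or uncorrected Pearson |z| ≥ 1.96.

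| Control v intervention | Stated | Pearson | Fisher | Fisher minus stated |
|---|---|---|---|---|
| 70% v 83% | 80% | 79.1% | 74.9% | −5.1 points |
| 70% v 85% | 90% | 90.3% | 87.7% | −2.3 points |
| 70% v 70% (true size) | not given | 5.0% | 3.8% | not applicable |

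As a cross-check, subtracting the continuity correction 1/160 = 0.00625 from the difference in Step 1 gives 74.5% and 87.2%, close to the Fisher values.

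**Step 3. The loss in other units.** With Fisher's test at 160 per arm, 80% power is reached at an intervention rate of about 83.8% and 90% power at about 85.5%. Keeping 83% and 85% as the detectable rates would need about 180 and 172 donors per arm. Switching to Pearson's test recovers 79.1 − 74.9 = 4.2 points and 90.3 − 87.7 = 2.6 points with no added donors.

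**Step 4. Are the cells small?** The smallest expected count per arm is n(1 − p̄): 160 × 0.235 = 37.6 for 70% v 83%, and 160 × 0.225 = 36.0 for 70% v 85%. The usual threshold for preferring an exact test is 5.

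**The case against.** The strongest reply is that the power statement may be correct as it stands. Study design words the primary outcome as compliance at every visit, which is the composite. The composite is tested with Pearson's test, and for that test 80% and 90% reproduce. This stands: the shortfall exists only if the 70% is a per-visit rate, and the article does not settle that. A reader might infer that the sample size calculation is simply wrong or that the trial is underpowered; the document does not support either. The reply does not remove the point, because the power statement is not limited to the composite, and the Statistical analysis section can be read as making the visit-level outcomes primary.

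Second, Fisher's test is valid at any sample size and errs on the safe side for type I error, and in terms of detectable rate the cost is under one percentage point (83.8% against 83%, 85.5% against 85%). That is also true, and it keeps the point modest. The article's remark that power was not the motive concerns the choice of outcomes, so it does not explain the choice of test.

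Third, the sentence that prescribes Fisher's test also covers center-level compliance. With two hospitals those counts are tiny, so it would be wrong to say that an exact test has no use in this plan. The cell-size argument applies to donor-level rates only.

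A reader might also conclude that visit and composite p-values cannot be compared because the tests differ. That goes too far: both are accepted tests at the nominal level (true size 3.8% and 5.0% here), and the endpoints differ in any case.

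**Conclusion.** The concern holds in conditional form. At two-sided 5%, the stated powers belong to Pearson's chi-squared test, which the plan uses only for the three-visit composite. If 70% is a per-visit control rate, the planned Fisher tests have about 75% and 88% power instead of 80% and 90%, with a true type I error near 3.8% at a common rate of 70%. If 70% is the composite rate, the stated figures are right to rounding, and the article then gives no power figure for the visit-level tests.

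The conclusion rests on two assumptions that the article does not confirm: the alpha and sidedness, and the endpoint to which 70% belongs. The gap between 79% under Pearson's test and the stated 80% is rounding and needs no correction. The effect is modest and does not threaten the validity of the trial. It is worth correcting because the mismatch can be removed at no cost in donors.

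**What to change.** 1. In Statistical analysis, use Pearson's chi-squared test for the donor-level comparison at each visit, as already planned for the composite. Keep an exact test only where expected counts are small, for example center-level comparisons. A site-stratified test is not needed to resolve this point.
2. In Sample size calculation, state the endpoint to which the 70% belongs (single visit or all three), the test assumed, and the alpha with its sidedness.
3. If Fisher's test is kept for the visits and 70% is a per-visit rate, restate the visit-level power as about 75% at 83% and 88% at 85%.

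The cost is a few sentences of wording. No donors, visits or data items are added.

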**Fig. 2 Fig2:**
[figure not shown]
Power calculation of evaluating the effectiveness of the financial incentive intervention with 320 donors enrolled at MDJH and MDUM over 4 years

### Ethics and dissemination

#### Research ethics approval

This study was approved by the Johns Hopkins School of Medicine IRB (IRB00126158) and the University of Maryland Medical Center IRB (HP-00081637). Amendments to the protocol will be submitted to the Johns Hopkins School of Medicine and University of Maryland Medical Center IRBs for review and approval. Subsequent to initial review and approval, the responsible local IRBs will review the protocol at least annually. Participants will be notified of any significant changes to the study design via a mailed letter using the information collected at the time of recruitment. The clinical and research activities being reported are consistent with the Declaration of Helsinki and Declaration of Istanbul.

#### Participant and data confidentiality

Only requisite study personnel at MDJH and MDUM will have access to identifying patient information. Johns Hopkins study team members will receive data about whether patients enrolled in the RCT at MDUM completed their required 6-month, 1-year, and 2-year follow-up visits but will have no direct patient contact with these donors. Study data will be collected and managed using REDCap electronic data capture tools hosted at Johns Hopkins University [32]. Data will be stored on the REDCap server for 7 years according to HIPAA requirements. All study personnel have received requisite training in data confidentiality and human subjects research.

#### Data safety and trial monitoring

The Johns Hopkins School of Medicine IRB determined that a data monitoring committee was not necessary for this RCT due to minimal participant risk. Data monitoring will be conducted and reported by the PI as projected by the data safety monitoring plan. The PI will immediately report any unanticipated adverse events or study deviations to the Johns Hopkins School of Medicine IRB.

#### Dissemination plan

Summary results of this RCT will be reported to ClinicalTrials.gov no later than 1 year after the study completion date, as per the NIH Policy on Dissemination of NIH-Funded Clinical Trial Information [33]. We also anticipate submitting the findings of this pilot RCT for peer-reviewed publication. Authorship eligibility will be determined using ICJME guidelines [34].

## Discussion

This randomized controlled trial will provide valuable information about whether using small financial incentives is an effective strategy to promote patient compliance with donor follow-up. If financial incentivization proves to be effective in this setting, the results of this RCT could serve as evidence to guide potential center-level and national initiatives to provide financial incentives for all live kidney donors. On the other hand, if financial incentivization does not effectively improve compliance, this will suggest that alternative interventions to increase live donor engagement with post-donation follow-up care should be explored.

This RCT has several limitations which merit discussion. Historically, donors have been predominantly Caucasian [5, 35]. In 2016, Caucasian donors donated 70% of living donor kidneys in the United States [5]; comparatively, 77% of the donors in our cohort are Caucasian. As such, our results may have limited generalizability to minority populations (ex: African American, Hispanic, and Asian donors). In addition, because the gift cards are mailed to participants assigned to the intervention arm rather than distributed in person, it is possible that some may not reach the intended recipient. However, we will use USPS Certified Mail, which requires a signature by the recipient for delivery, and will record any delivery failures. Finally, it is possible that unblinded intervention arm assignment could result in ascertainment bias; however, it would be infeasible to blind study participants in this RCT, as the intervention is dependent on the participant’s expectation of a financial incentive for follow-up completion.

Despite the aforementioned limitations, this trial has several key strengths. To our knowledge, it is the first clinical trial to assess the effectiveness of using financial incentives to promote donor compliance with postdonation monitoring efforts by a transplant hospital. Additionally, our randomized design will provide high-quality evidence to inform center-level and national efforts to improve donor follow-up compliance. If found to be effective, financial incentivization could serve as a useful strategy in center-level and national initiatives to improve postdonation care for live kidney donors.

## Data Availability

Not applicable.

## Abbreviations

IRB: Institutional review board
MDJH: Johns Hopkins Hospital Comprehensive Transplant Center
MDUM: University of Maryland Medical Center Transplant Center
RCT: Randomized controlled trial
LDKT: Live donor kidney transplantation
ESRD: End-stage renal disease
OPTN: Organ Procurement and Transplantation Network
